## Assignment of interventions: allocation

### Sequence generation {16a}

After verification of the eligibility criteria, family’s information, and consent signature, each participant will be randomized. Intervention allocation will be done using a computer-based random number generator. Randomization will be performed as soon as the number of participants is reached to start a session (one CBT group and one TBI group) with a 1:1 ratio.

Randomization will be stratified by school level (primary vs middle school) and severity of psychopathological disorders using the CBCL A-A-A score. Children will be divided in groups according to their school level (< 11 years, and 11–13 years of age).

The investigator in charge of the study assessments is blinded to the group allocation.

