## Statistical methods

### Statistical methods for the primary and secondary outcomes {20a}

An intention-to-treat approach will be used to analyze the primary and secondary data from the trial. Participants will be analyzed in their randomization arm and cannot change group during the study.

The primary outcome measure is the changes of the “Aggressive behavior” sub-score between T1 (baseline) and T3 (month 6 post-intervention). A *Z* test will be used to compare the changes of the primary (between T1 and T3) and secondary outcomes (between T1 and T2/T3) in the CBT group and TBI group. In the case of group non-comparability, a multivariate model by linear regression could be carried out to take into account the potential confounding bias.

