### Interim analyses {21b}

In this trial, statistical analyses of data will be realized when the statistician will have all data (i.e., when the number of subjects required will be reached and when all visits will have been carried out).

The final decision to finish the trial will be taken by mutual agreement of the principal investigator, the data manager, the research coordinator, and the independent safety monitor. Data will be locked when all data have been checked and all corrections done.

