### Methods for additional analyses (e.g., subgroup analyses) {20b}

In the case of non-comparability for one or more parameters, an adjustment will be made on this/these parameter(s) for analysis of the judgment criteria. A multivariate linear regression model might be performed to account for potential confounders.

The protocol does not plan analyses for additional subgroups.

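### The primary analysis is an unadjusted change-score Z test, with regression only if the arms prove non-comparable; one pre-specified baseline-adjusted model would remove the discretion and gain precision.

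*Protocol article*

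**What the plan says.** Under Statistical methods {20a}, the primary outcome is the change in the Aggressive behavior sub-score from T1 to T3, and a Z "test will be used to compare the changes of the primary (between T1 and T3) and secondary outcomes". No covariate enters this test. The same section then adds: "In the case of group non-comparability, a multivariate model by linear regression could be carried out to take into account the potential confounding bias".

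Methods for additional analyses {20b} returns to the subject twice. First: "In the case of non-comparability for one or more parameters, an adjustment will be made on this/these parameter(s) for analysis of the judgment criteria". Then: "A multivariate linear regression model might be performed to account for potential confounders". The adjustment is thus permitted in {20a}, required in the first sentence of {20b}, and permitted again in the second.

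On timing, Interim analyses {21b} says that "statistical analyses of data will be realized when the statistician will have all data". On design, Sequence generation {16a} says: "Randomization will be stratified by school level (primary vs middle school) and severity of psychopathological disorders using the CBCL A-A-A score". The description of the CBCL shows that the A-A-A score is a sum of three subscale T-scores, one of which is the primary outcome.

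**The concern.** Two things are at stake.

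The first is which result counts as primary. The article gives no criterion for non-comparability and names no candidate covariates. It does not say whether the adjusted result replaces the Z test or sits beside it. The three sentences on adjustment disagree about whether it happens at all. Because the analyses come after all data are in, the choice can be made with both results in view.

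The second is precision. The default analysis ignores the correlation between the baseline and month-6 scores except by subtraction, and it ignores the two factors on which randomisation was stratified. In a trial of 68 children that gives away information already being collected.

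**Working it through.** **Inputs.** From Sample size {14}: expected month-6 scores of 65 and 69 (difference 4), common SD 5.5, power 80%, alpha 5%, 31 per group, 68 in total after a 10% increase. The correlation r between the T1 and T3 scores is not given, so a range is assumed. Equal SDs at both visits are also assumed.

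**The plan's own figure.** The two-sided normal formula gives n = 2 × (5.5 × (1.960 + 0.842) / 4)² = 29.7, so 30 per group. The noncentral t gives 79.1% power at 30 and 80.4% at 31, so 31 reproduces. Then 31 × 1.10 = 34.1, giving 34 per group and 68 in total. The SD used is that of the month-6 score, whereas the planned test is on change. The two SDs coincide only at r = 0.5, since 5.5 × √(2 × 0.5) = 5.5.

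**Precision.** SD of change = 5.5 × √(2(1 − r)). Residual SD after baseline adjustment (ANCOVA) = 5.5 × √(1 − r²). The ratio of ANCOVA to change-score variance is (1 + r)/2. Power below is for a two-sided t test of 4 points at 31 per arm.

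| r | SD of change | ANCOVA SD | variance ratio | power, change | power, ANCOVA |
|---|---|---|---|---|---|
| 0.3 | 6.51 | 5.25 | 0.65 | 66% | 84% |
| 0.5 | 5.50 | 4.76 | 0.75 | 80% | 90% |
| 0.7 | 4.26 | 3.93 | 0.85 | 95% | 98% |

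With a normal reference, as the article specifies, the change-score powers are 67.7%, 81.7% and 95.9%. At r = 0.8 the normal-reference powers are 99.5% and 99.8%, so the gain has vanished. At r = 0.5 the variance saving is 25%, equivalent to 1/0.75 = 1.33 times as many children.

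**Discretion.** Null trials were simulated with 31 per arm and complete data, 10,000 runs per value of r. The baseline score and four unrelated baseline variables were available for checking.

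| r | Z test on change | baseline-adjusted | mechanical rule | either result significant |
|---|---|---|---|---|
| 0.3 | 5.5% | 4.9% | 4.5% | 8.2% |
| 0.5 | 5.8% | 5.1% | 5.0% | 7.8% |
| 0.7 | 5.5% | 5.0% | 5.2% | 7.1% |

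The mechanical rule adjusts for any of the five variables that differ at p < 0.05 and otherwise keeps the Z test. It was triggered in 22 to 23% of null trials. The last column is the worst case for two results: the favourable one is always reported.

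**Smaller points.** A 1.96 cut-off with an estimated SD on 60 degrees of freedom has a true two-sided level of 5.46%. Under simple randomisation with 34 per arm, the SE of the baseline difference is 5.5 × √(2/34) = 1.33, so a gap above 1 point has probability 0.45. Each point of gap moves the change-score contrast by (1 − r) relative to ANCOVA, which is 0.5 point at r = 0.5. Because A-A-A is a stratification factor, 0.45 is an upper value. With two equal strata, balance within strata, and a correlation of 0.5 to 0.7 between aggression and A-A-A (all assumed), the SE falls to about 1.22 to 1.11 and the probability to about 41 to 37%.

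**The case against.** The best defence is that a default exists. {20a} says firmly that the Z test will be used, and the fuller adjustment text sits under additional analyses. On that reading the primary test is fixed and regression is supplementary, while thresholds and covariate lists belong in an analysis plan that is not shown. This has some force, but the first sentence of {20b} applies a mandatory adjustment to the outcome analyses themselves, which contradicts a purely supplementary role. The objection here is to a rule that the article states, not to a missing detail.

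It is also right that a change-score comparison is valid under randomisation, so the issue is efficiency. At r = 0.5 the planned test has the power it was designed for. A shortfall needs r below 0.5, and the article gives no r.

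Four stronger readings are tempting, and the documents do not support them:

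- A reader might infer that any adjustment triggered by imbalance inflates the error. The simulation shows that a mechanical rule does not.
- A reader might infer that leaving out the strata produces false positives. Omitting prognostic strata tends to make the standard error too large, which is conservative.
- A reader might infer that medication changes after randomisation could become covariates, because they are recorded for their possible influence on outcomes. No passage plans this, and group non-comparability most naturally means baseline differences.
- A reader might make much of Z against t. The difference is 5.5% against 5.0%, and the planned multiple imputation means that 60 degrees of freedom is itself only an approximation.

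**Conclusion.** The point holds as a should-fix. The article states an unadjusted default and a data-triggered alternative with conflicting force, so it does not define one primary result. Where the choice between the unadjusted and baseline-adjusted results is free, type I error is about 7 to 8%. Part of that is the Z cut-off, since the Z test alone runs at 5.5 to 5.8% in the same simulation.

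The precision loss is certain in direction for any r below 1, given equal SDs. Its size rests on the assumed r: large at 0.3, moderate at 0.5, negligible at 0.8 or more. An actual power shortfall is not shown. What can be said is that at 31 per arm ANCOVA keeps about 80% power or better for any r of zero or above, whereas the change-score test does so only from about r = 0.5.

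**What to change.** Pre-specify one primary analysis, to be used whatever balance is observed: a linear model of the T3 Aggressive behavior score on arm, with T1 Aggressive behavior score, school level and the A-A-A stratum used at randomisation as covariates. Inference should be t-based and pooled over the planned imputations. Delete the non-comparability trigger from both {20a} and {20b}. Keep the unadjusted comparison of changes as a labelled sensitivity analysis.

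The cost is wording in two sections and in any analysis plan, submitted as a protocol modification under {25}. Every covariate is already collected before randomisation. Since {21b} defers all analyses until the data are complete, the change can be dated and documented before any result is known.

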### Interim analyses {21b}

In this trial, statistical analyses of data will be realized when the statistician will have all data (i.e., when the number of subjects required will be reached and when all visits will have been carried out).

The final decision to finish the trial will be taken by mutual agreement of the principal investigator, the data manager, the research coordinator, and the independent safety monitor. Data will be locked when all data have been checked and all corrections done.

### Methods for additional analyses (e.g., subgroup analyses) {20b}

In the case of non-comparability for one or more parameters, an adjustment will be made on this/these parameter(s) for analysis of the judgment criteria. A multivariate linear regression model might be performed to account for potential confounders.

The protocol does not plan analyses for additional subgroups.

### Methods in analysis to handle protocol non-adherence and any statistical methods to handle missing data {20c}

Analysis of the primary and secondary outcomes will be carried out per protocol for all families who participated in two thirds of the intervention.

For missing data, under the hypothesis of a Missing at Random (MAR) or Missing Completely at Random (MCAR) mechanism, an imputation method using the Markov chain Monte-Carlo method will be used with 15 imputation cycles. The analysis will be performed independently for each complete database and the results will be taken into account for estimating the final parameters and their standard deviations.

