### Trial design {8}

The study described in this protocol is a randomized controlled trial to evaluate the superiority of a CBT program for children with ADHD and ED compared with the TBI program. Sixty-eight children with ADHD and ED will be randomized (1:1) in the CBT or TBI group. Randomization will be stratified by school level and by the psychopathological disorder severity using the Child Behavior Checklist-A-A-A (combination of “Aggression,” “Anxiety/Depression,” and “Attention” subscales). Children will be divided in groups according to their school level: primary school (younger than 11 years) and middle school (11–13 years of age). This classification is required because the situations encountered in everyday life are not the same in middle and primary school.

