### Sample size {14}

As ED in children with ADHD has been only recently studied, it is difficult to find literature data for calculating the number of subjects required (particularly for assessing the changes in the “Aggressive behaviors,” “Anxiety/Depression,” and “Attentional Problems” scores of the CBCL scale).

The study by Masi et al [54]. reported a change in the “Aggressive behavior” score of the CBCL from 68.3 to 65.5 in the context of the non-comparative evaluation of an intervention similar to the one assessed in the present trial. The standard deviation of the score at the baseline was 5.4.

By making the reasonable assumption of a slightly more effective intervention than what reported by Masi et al [55]., a CBCL score of 65 in the intervention group and 69 in the control group, with a common standard deviation of 5.5, can be expected at month 6 post-intervention. To highlight such a difference with a power of 80% and an alpha risk of 5%, 31 subjects per group need to be included. By increasing this number by 10% to take into account participants lost to follow-up, the total number of subjects to be included in the study is 68 (34 per group).

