## Trial status

Protocol version: August 8, 2018 Version n°3.

Date of recruitment: June, 2017

End of recruitment: September, 2020

The article was submitted after the end of recruitment and not at the beginning: with the co-authors, we favored the implementation of research (doctors' information for recruitment, animation of groups) as well as the writing of a background article that has been published. In addition, due to the pandemic, several participants of the last group dropped out of the study. We had the agreements of the methodologist and the research assistant to extend recruitments and continue the study with another session. Research is currently underway as patients are still participating in groups.

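### Intention-to-treat and a two-thirds-attendance per-protocol analysis are both prescribed for the same primary and secondary outcomes, and the protocol does not say which one decides the trial

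*Protocol article*

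**What the plan says.** The design is a "randomized controlled trial to evaluate the superiority of a CBT program for children with ADHD and ED compared with the TBI program" (Trial design {8}), with 68 children allocated 1:1.

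Two sections of the protocol article name the analysis population:

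- **Statistical methods {20a}:** "An intention-to-treat approach will be used to analyze the primary and secondary data from the trial". It continues: "Participants will be analyzed in their randomization arm and cannot change group during the study".
- **Section {20c}, on non-adherence and missing values, reads:** "Analysis of the primary and secondary outcomes will be carried out per protocol for all families who participated in two thirds of the intervention".

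Section {20c} then plans multiple imputation by Markov chain Monte Carlo with 15 cycles, without saying to which population it applies. The section on additional analyses {20b} covers adjustment for non-comparability and does not mention per protocol.

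The primary outcome is the change in CBCL Aggressive behavior from baseline to month 6 after the intervention (Outcomes {12}). Reasons for stopping the allocated intervention, or for leaving the programme, include disruptive behaviour, behaviour not stabilised by drugs, aggression toward others and strong opposition to taking part (sections {11b} and {30}).

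**The concern.** Both sentences are flat statements of what will be done, and both cover the primary and the secondary outcomes. If the two analyses disagree, the document gives no basis for saying which one answers the trial's question, and the choice could be made after the results are known.

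The two analyses do not carry equal weight in a superiority trial. Intention-to-treat keeps the comparison that randomisation created. A set defined by attendance is formed afterwards, and here some of the reasons for poor attendance are close to what the primary outcome measures. A child removed for aggression early in the programme would drop out of the two-thirds set, possibly in different numbers or for different reasons in the two arms.

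**Working it through.** **Step 1. The two statements side by side.**

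| | Section {20a} | Section {20c} |
|---|---|---|
| Outcomes | primary and secondary | primary and secondary |
| Population | intention-to-treat, arm as randomised | families with two-thirds participation |
| Called primary? | no | no |
| Called supportive, additional or sensitivity? | no | no |

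The outcomes are the same, the populations differ, and no order is given.

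**Step 2. Can membership of the per-protocol set depend on the outcome trait?** Attendance is recorded session by session after allocation ({18a}). Sections {11b} and {30} let aggression or unstabilised behaviour end participation. The primary outcome is an aggression score. The link is therefore possible under the protocol's own rules. The removal rules are the same in both arms, and no attendance data by arm are given, so neither a difference between arms nor its direction can be derived.

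**Step 3. What two thirds means.** The children have 15 sessions and the parents 8 (Abstract, Methods).

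- Child sessions: 15 × 2/3 = 10.
- Parent sessions: 8 × 2/3 = 5.33, so 6 or more in practice.

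Either rule can be applied. The text speaks of families and does not say whether child sessions, parent sessions or both count.

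**Step 4. Reproduce the planned sample size.** Inputs from Sample size {14}: "a CBCL score of 65 in the intervention group and 69 in the control group, with a common standard deviation of 5.5", 80% power and alpha 5%. Sidedness is not stated; two-sided is assumed.

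- Standardised difference: (69 − 65)/5.5 = 4/5.5 = 0.727.
- Normal approximation: n = 2 × (1.960 + 0.842)² × (5.5/4)² ≈ 29.7, so 30 per group.
- Two-sample t-test: 30.67, so 31 per group, which matches the plan.
- Inflation: 31 × 1.10 = 34.1, stated as 34 per group, 68 in total.

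The 10% is an allowance for loss to follow-up, not for low attendance.

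**Step 5. Illustration of power in a reduced set.** The documents give no attendance rate, so 20-30% of families below two thirds is an assumption.

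- 20%: 68 × 0.80 = 54.4, about 27 per arm.
- 30%: 68 × 0.70 = 47.6, about 24 per arm.

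Two-sided t-test power for 4/5.5:

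| Per arm | Power |
|---|---|
| 34 (all randomised, no loss) | 84.0% |
| 31 (planned) | 80.4% |
| 30 | 79.1% |
| 27 | 74.6% |
| 24 | 69.4% |

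The fair reference is the planned 31, so the fall would be from about 80% to 69-75%. This takes the same difference and SD to hold among attenders, which is itself unknown.

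**The case against.** The best counter-reading is that {20c} falls under the heading for protocol non-adherence, where a secondary, adherence-based analysis would normally be described, while {20a} is the main methods section and states intention-to-treat first. Other parts fit that reading: families who stop are to be asked for their final questionnaires ({18b}), and missing data are to be imputed ({20c}). The article is also condensed, and an analysis plan that is not shown may give the ranking. This makes a missing label likelier than a deliberate choice of per protocol as primary. It does not remove the problem: the sentence in {20c} is unqualified and conflicts, as written, with {20a}.

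Several stronger readings do not hold:

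- A reader might infer that the two-thirds threshold cannot be applied because 5.33 is not a whole number. It can, as 6 or more, and attendance of parents and child is recorded at each session.
- A reader might infer that the pandemic dropouts fall outside the per-protocol set and were replaced. Trial status says that "several participants of the last group dropped out of the study" and that recruitment was extended with another session. It does not say how many sessions those families had attended, or that anyone is replaced or excluded from analysis. They may or may not meet the threshold.
- A reader might infer that CBT and theatre will lose different kinds of children. The content differs, but differential selection is a possibility and is not shown.
- The power figures matter only if the per-protocol set were primary. A supportive analysis need not have 80% power.

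**Conclusion.** The concern holds as a conflict between two sections. The same outcomes are assigned to two populations and neither is named as decisive. Under the protocol's own removal rules, using the two-thirds set as primary would open the superiority comparison to selection on a trait related to the primary outcome.

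The bias cannot be sized or signed from the document. The power illustration (69-75% at 24-27 per arm, against 80% at 31) depends on an assumed 20-30% of families below the threshold and on an unchanged difference and SD. The effect of the pandemic dropouts likewise depends on attendance that is not reported. The document does not support saying that per protocol has been chosen as primary, or that bias will occur.

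**What to change.** In {20a}, state that the sole primary analysis is intention-to-treat in all randomised children, including those who left or were removed from the groups, using the multiple imputation already planned. In {20c}, say that the imputation serves this analysis, relabel the two-thirds analysis as supportive, and state whether child sessions, parent sessions or both count toward the threshold.

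The cost is a few sentences, mirrored in the analysis plan. No new data are needed: final questionnaires are already sought from families who stop ({18b}) and attendance is already recorded ({18a}). Analysis is to wait until all visits are complete ({21b}), and groups were still running when the article was written (Trial status), so the wording should be settled before the data are locked.

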### Plans to give access to the full protocol, participant-level data, and statistical code {31c}

On request, participants will be informed about the trial overall results by the principal investigator. Families will not have access to personal data.

## Oversight and monitoring

### Composition of the coordinating center and trial steering committee {5d}

Data monitoring committee is composed of a research assistant who ensures compliance with progress of research protocol and regulatory aspects. Data collection and management and statistical analyses are carried out by Department of Medical Information (DMI) of Montpellier University which is made up of a methodologist, a statistician, and a data manager. Daily, groups are led by psychologists, nurses, and educators. Blind evaluations are carried out by a psychologist who recruit participants, collects data, and leads interventions. Two doctors, including principal investigator, sign consents.

